### Strategies to improve adherence to interventions {11c}

Not applicable as the intervention is performed only once, intraoperatively. Adherence to the follow-up visit schedule is promoted by facilitating the last two study visits 10 and 30 days postoperatively as a structured telephone interview. Furthermore, all study procedures and visits closely orientate towards standard medical care.

### Relevant concomitant care permitted or prohibited during the trial {11d}

No additional treatments or interventions will be performed within the study. All patients will receive standard perioperative antibiotic prophylaxis, the timing and type of which will be recorded in the eCRF. Furthermore, the application of abdominal wall protectors is recommended for contaminated procedures and must be recorded in the eCRF. A change of gloves ahead of wound closure is frequently performed in contaminated procedures and must also be recorded in the eCRF. If an irrigation-suction-drain is placed in the abdominal cavity and the patient receives prophylactic intraabdominal irrigation therapy via this device postoperatively, the patient must be excluded from the study. If indicated for medical reasons, all kind of medication is permitted during the study. Postoperative medication with known adverse effects on wound healing (e.g. antibiotics, corticoids, and other immunosuppressive agents) will be recorded in the eCRF. Any operative or interventional revision of the wound will be documented as AE/ SAE in the eCRF.

### Provisions for post-trial care {30}

Not applicable as no additional risks and harms from study participation are anticipated, and no additional travel is necessary for the patient.

### Outcomes {12}

The primary efficacy endpoint of the study is occurrence of SSI within 30 days postoperatively, according to the internationally accepted and recommended SSI definition by the CDC (Table 1) [6]. This endpoint has been used in previous studies and assures comparability of the results [8–10, 25]. This endpoint is further considered to be of clinical relevance as SSI increases morbidity and mortality of individual patients, direct and indirect costs and prolongs hospital stay as outlined before. The duration of hospital stay is considered as a secondary outcome, in order to evaluate the potential economic benefit of the intervention. In addition, the following outcome measures have been defined as secondary endpoint measures and will be determined by the unit given in parentheses:Rate of SSI by CDC class I–III (superficial, deep, organ-space) (%)Duration of hospital stay up to 30 days after surgery (days);30 days mortality (%);30 days rate of reoperation/relaparotomy (%);30 days rate of postoperative complications in both groups (%). All AE/SAEs will be additionally classified according to the Clavien-Dindo classification of surgical complications and the Comprehensive Complication Index [26, 27].

### Participant timeline {13}

Figure 1 and Table 3 reflect the intervention scheme flow and visits for the PAISI study. Visits are the same for all participants of the study, regardless of the intervention group.

**Fig. 1 Fig1:**
[figure not shown]
PAISI intervention flow scheme (according to SPIRIT statement 2013 [28])

**Table 3 Tab3:** PAISI study visits (according to SPIRIT statement 2013 [28])

	Study period				
	Inclu.	Rand.	Post-allocation		Close-out
Study visit Number	1	2	3	4	5
Timepoint	− 1–3 days	day 0)	day 5	day 10 (+5)	day 30 (+5)
Informed consent	X				
Inclusion and exclusion criteria	X				
Randomization		X			
Intervention (IPI with 1500ml NaOCl/HOCl solution)		X			
Control (IPI with 1500ml Ringer solution)		X			
Demographical data	X				
Medical history and Charlson Comorbidity Index	X				
Medication with known effects on wound healing	X				
Physical examination	X				
Type of operation		X			
Duration of operation		X			
Level of contamination		X			
Type and length of incision		X			
Abdominal wall closure technique and suture material		X			
Presence of an enterostomy		X			
Use of wound edge protectors		X			
Changing of gloves		X			
Placement and type of-intra-abd. drains		X			
Postoperative medication with known effects on wound healing			X	X	X
Documentation of SSI			X	X	X
Documentation of other postoperative complications (Clavien Dindo and CCI)			X	X	X
Documentation of re-operation			X	X	X
Documentation of postoperative intra-abd. irrigation via irrigation-suction drainage system			X	X	X
Documentation of AE/SAE of special interest		X	X	X	X
Duration of hospital stay					X

### Sample size {14}

The sample size was calculated (nQuery 8 software, version 8.6.1.0, Statistical Solutions Ltd, Cork, Ireland) based on the primary endpoint of the study. Assuming SSI rates of 4% and 16% for the experimental and the standard group respectively (OR=4.571), the one-sided z-test (Group Sequential test of two proportions) at the 2.5% significance level with a total of two looks at the data will have overall 80% power to show superiority of the experimental over the standard arm if the study includes at least 232 patients (116 patients per intervention group). The calculation is continuity corrected due to the expected low proportion in the experimental group. The results assume that the group sequential design has one interim sequential test for monitoring and sample size re-estimation (two total looks at the data including final analysis), which means that an interim analysis is planned after half of the patients have reached 30 days post-surgery. The O’Brien-Fleming spending function is used to determine the efficacy test boundary and the non-binding futility boundary. The group sequential test boundaries (Z scale) for the interim and the final analysis are as follows:

Upper efficacy bounds: 2.963 and 1.969

Futility bounds: 0.555 (non-binding) and 1.1969.

A drop-out rate of about 20% is expected in this study, based on experience from similar trials previously conducted within the CHIR-*Net* trial network. Therefore, a total of 290 patients (145 per intervention group) should be included in the study.

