	**…or the infection is diagnosed by the attending surgeon**

### Trial design {8}

This is a prospective, randomized, controlled, observer and patient-blinded, single-centre, two-arm surgical study with an adaptive parallel groups design. Pre-screening of potential patients (evaluation of inclusion and exclusion criteria) is possible up to 14 days prior to the planned procedure. Patients can be included if inclusion and exclusion criteria apply and written informed consent is provided. Included patients are randomized to peritoneal and epifascial wound irrigation with NaOCl/HOCl (50/50ppm) or Ringer solution. A reduction of 30-day postoperative SSI I–III rates by lavage with NaOCl/HOCl solution is postulated. Since there is currently no data on incidence rates from randomized clinical trials, the rates for sample size calculation were estimated according to the clinical experience at our institution. Therefore, the study is designed with one unblinded look at the data, which will be performed after half of the patients reached the primary endpoint (30 days post-surgery), by a second study statistician, who will not participate in the final study analysis. This interim information will be used to check the assumptions which were used to calculate the sample size for the study. If needed, the sample size will be adjusted.

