## Statistical methods

### Statistical methods for primary and secondary outcomes {20a}

The intention-to-treat (ITT) set consists of all patients who received irrigation of the abdominal cavity before closure of the abdominal fascia with one of the study solutions. Analysis will be performed as randomized regardless of the actual intervention and regardless of any further medical or surgical treatments. The Per-Protocol (PP) set consists of patients treated according to protocol, excluding any major protocol violations. The PP set will be analysed as treated. The Safety (SA) set will consist of all patients in the ITT set, analysed as treated.

All primary and secondary analyses will be performed on the ITT set. Sensitivity analysis of the primary endpoint will be performed on the PP set. The SA set will be used for the safety analyses. The incidence of SSI within 30 days after surgery will be compared between the two study groups using the one-sided group sequential test of two proportions at the 2.5% significance level with a total of two looks at the data. The primary endpoint analysis will be performed on the ITT set. Since the ITT set includes all patients who were treated in the study regardless of any further medical or surgical treatments, it is expected, that the SSI rates 30 days post-surgery will be available for most patients. Nevertheless, it is possible that some patients do not reach the primary endpoint due to death, withdrawal of informed consent, loss to follow-up, or other unforeseen reasons. Patients who die before day 30 will be considered as having SSI at time of death regardless of the intervention group, unless SSI was documented earlier. All other missing primary endpoint data will be dealt with using multiple imputations based on binary logistic regression models including LOC, ASA, BMI, age, diabetes, type of surgery, duration of surgery, use of wound-edge protectors, and intraoperative changing of gloves.

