### Interim analyses {21b}

Thirty days after the first half of the patients has reached the primary endpoint, an interim analysis will be performed by a second statistician, who does not take part in the final study analysis. A decision will be made by the study leadership, using the blinded results to stop the study with proven efficacy, stop the study for futility, continue the study as planned, or continue the study after adjusting the sample size.

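### The sample size may be changed after an unblinded interim look with no rule and no matching final test, so the one-sided 2.5% error rate is not guaranteed

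*Protocol article*

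**What the plan says.** Four sections of the protocol article bear on this.

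- Sample size {14} gives the single interim look two jobs: "one interim sequential test for monitoring and sample size re-estimation (two total looks at the data including final analysis"). It comes when half of the patients have reached 30 days. The efficacy bounds on the Z scale are 2.963 and 1.969. The interim futility bound, 0.555, is labelled non-binding.
- Trial design {8} states that "the study is designed with one unblinded look at the data", taken by a second statistician. The purpose is to check the sample size assumptions, and the size is adjusted if needed. The Methods part of the abstract says the same.
- Interim analyses {21b} lists the options open to the study leadership. One is to "continue the study after adjusting the sample size". The same sentence describes the results they use as blinded.
- Statistical methods {20a} names the primary analysis: the "one-sided group sequential test of two proportions at the 2.5% significance level with a total of two looks at the data".

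No section states a re-estimation rule, whether the size may fall as well as rise, a maximum, a weighted or combination statistic, or a recalculated final bound.

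**The concern.** The bound 1.969 comes from the joint distribution of the interim and final Z when the interim carries exactly half of the final information. If the second-stage size is chosen after seeing the treatment difference, the ordinary final Z no longer has that distribution. A weak interim result can be diluted by adding patients, and a strong one can be protected by adding few. The printed bounds do not cover the adjustment that the plan also permits.

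At stake is the type I error of the one confirmatory test. If the size is changed and the final result is positive, a critic could fairly say that the 2.5% level was never secured. No data monitoring committee is planned (section {21a}), and the study leadership takes the decision, so nothing outside the written rule limits the choice.

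**Working it through.** **Inputs, all from Sample size {14}.** One-sided 2.5%, two looks, interim at information fraction 0.5, O'Brien-Fleming spending, 80% power, SSI rates of 4% and 16%, 116 per arm, continuity corrected.

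**1. Reproducing the plan.** Alpha spent at the interim is 2[1 − Φ(2.2414/√0.5)] = 0.001525, which gives a bound of 2.963. Bivariate normal integration with correlation √0.5 then gives a final bound of 1.969. For the size, the drift for 80% power with O'Brien-Fleming futility spending is 2.879, and the variance sum is 0.04 × 0.96 + 0.16 × 0.84 = 0.1728. So n = 2.879² × 0.1728 / 0.12² = 99.5 per arm. The continuity correction makes this (99.5/4) × [1 + √(1 + 4/(99.5 × 0.12))]² = 115.5, so 116 per arm and 232 in all. The stated design is sound as a fixed two-stage design.

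**2. Error rate with a changed size.** Let R be the final size divided by the planned size, so that the interim fraction becomes t = 0.5/R. Under the null, given interim z₁ below 2.963, the ordinary final test rejects with probability

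A(z₁, R) = 1 − Φ[(1.969 − √t · z₁)/√(1 − t)].

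The total error is 1 − Φ(2.963) plus the integral of A(z₁, R(z₁)) φ(z₁) over z₁ below 2.963. With R = 1 throughout, this is 0.0015 + 0.0235 = 0.0250.

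**3. Why the rule matters.**
- At z₁ = 0.5 and planned size: (1.969 − 0.354)/0.707 = 2.285, so A = 1.1%. At double size (t = 0.25): (1.969 − 0.25)/0.866 = 1.985, so A = 2.4%. Adding patients raises the chance of a false positive.
- At z₁ = 2 the direction reverses: 21.6% at planned size and 13.2% at double size.
- For doubling, the two are equal at z₁ = 1.21, where conditional power at the observed trend is 36%.

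**4. Results under assumed rules.** The plan gives no rule, so every cap and floor here is an assumption. The observed-effect rule sets R = 0.5 × (2.80/z₁)², where 2.80 = 1.960 + 0.842, limited to the allowed range, with R at the cap when z₁ ≤ 0. Futility is not enforced unless stated.

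| Assumed rule | One-sided error |
|---|---|
| Observed effect, increases only, cap 1.5× / 2× / 4× | 2.8% / 3.0% / 3.3% |
| Observed effect, may also fall to 0.6×, cap 2× / 4× | 3.3% / 3.7% |
| Worst choice of R at each z₁, increases only, cap 1.5× / 2× / 3× | 2.9% / 3.1% / 3.3% |
| Worst choice of R, 0.6× to 2× | 3.9% |
| Increases only, to 80% conditional power, only if conditional power is at least 30% or 50%, caps 1.5× to 3× | 2.4–2.5% |
| Increases only, futility at 0.555 always obeyed, worst choice, caps up to 3× | 2.5% |
| 0.6× to 2×, futility always obeyed: observed effect / worst choice | 2.7% / 3.3% |

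**5. Pre-fixed weights.** With Z = √0.5 · Z(stage 1) + √0.5 · Z(stage 2), the stage 2 statistic is standard normal under the null whatever size was chosen. The joint distribution behind 2.963 and 1.969 is preserved, and the error is 2.50% under any rule.

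**The case against.** The strongest reply is that the article never says 1.969 is kept, unweighted, once the size has changed. It calls the design adaptive, and a weighted statistic or re-estimation rule could stand in the full protocol or an analysis plan that is not shown. A reader might infer that the trial will run the ordinary test after resizing and that the 2.5% claim is therefore false. The documents do not support that: the final statistic after a change is not stated, and several reasonable rules keep the error at or below 2.5%.

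Two further points have weight. Interim analyses {21b} speaks of blinded results, and resizing on pooled event rates alone would largely remove the problem. And the direction of an adjustment is not given. The text on power, "if the study includes at least 232 patients (116 patients per intervention group"), leans against going below 232, so the figures that rely on decreases are less secure.

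What remains is that the article does more than stay silent. It names a test, prints its bounds, claims an error rate, and permits an adjustment those bounds do not cover. Futility stopping cannot be counted on, because the bound is declared non-binding. The word blinded conflicts with the unblinded look in Trial design {8} and the abstract, and stopping for proven efficacy against 2.963 needs comparative results.

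**Conclusion.** The concern stands in a limited form: as written, the one-sided 2.5% level is not guaranteed. It is not shown to be broken. For increases only, with the ordinary test and futility not enforced, the plausible excess is modest: 2.8% to 3.3% under the observed-effect rule with caps from 1.5 to 4 times the planned size, and 3.1% at worst with a cap of 2. If the size may also fall to 0.6 times the plan, the worst case with a cap of 2 is 3.9%. Larger figures need a floor that leaves almost no second-stage patients and should not be used. The excess disappears if only increases are allowed and they are either confined to promising interim results or accompanied by strict futility stopping. All these figures rest on assumed rules and on the ordinary Z being kept at 1.969. The gap should be closed before interim results are seen, because a method chosen afterwards is hard to defend.

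**What to change.** Before the interim analysis, specify one of the following.

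1. Preferred: final statistic Z = √0.5 · Z(stage 1) + √0.5 · Z(stage 2), with stage 2 computed only from patients not in the interim data, tested against 1.969. Allow increases only, up to a stated maximum. If the size is unchanged, this is essentially the planned test.
2. Alternative: keep the ordinary test at 1.969, but state in advance that the size may only rise, up to a stated cap, and only within a conditional-power zone shown by calculation to keep 2.5%.

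In either case, reconcile the blinded results in Interim analyses {21b} with the unblinded look in Trial design {8} and the abstract. State who sees comparative data and what information drives the resizing. If resizing is meant to use only pooled event rates, say so.

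The cost is a paragraph in the protocol or analysis plan. The weighted test loses a little efficiency, and only if the size is changed.

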### Recruitment {15}

The recruitment period is expected to be approximately 32 months (first patient in, to last patient out 33 months). In the study site, an average of around 80 laparotomies LOC II–IV are performed per month. Experience from previous clinical studies shows that the recruitment of 10 patients per month is feasible here. To cover any unforeseen recruitment difficulties, for example due to the COVID-19 pandemic, 3 extra months of recruitment time were added. In the case of elective procedures, pre-screening (this is just a pre-selection of eligible patients within the study team) of patients can be performed up to 14 days prior to the scheduled surgical procedure. In case of emergency procedures, screening and inclusion can take place on the day of admission to the hospital, which is usually the same day as surgery.

## Assignment of interventions: allocation

### Sequence generation {16a}

The randomization list will be generated by an online randomization tool (Randomizer, Institute for Medical Informatics, Statistics and Documentation, Medical University of Graz, Austria; URL: http://www.randomizer.at). Online-Randomization will be performed at the end of the surgical procedure before the abdominal fascia is closed and will be stratified by LOC of the surgical procedure (LOC II–IV; Table 2). To assure balanced group sizes during the accrual, a block-wise randomization is applied.

### Concealment mechanism {16b}

Only designated members of the study team, who will not perform postoperative study visits, will have access to the online randomization tool. After informing the surgical team of the randomization result, the randomization sheets will be printed out and must be stored away from the patient records, study documents and ISF to ensure blinding of the rest of the local study team.

### Implementation {16c}

The allocation sequence is generated by the Randomizer tool (Institute for Medical Informatics, Statistics and Documentation, Medical University of Graz, Austria; URL: http://www.randomizer.at). Participants will be enrolled by the specifically trained medical doctors of the local study team. Participants will be assigned to the intervention groups by the designated study nurse or medical doctor who is effectuating the online randomization.

## Assignment of interventions: blinding

### Who will be blinded {17a}

The blinding procedure is restricted to participating patients, the statistician who performs the final analysis and the outcome assessors. Blinding of the surgical team that performs the intervention is impossible because of the distinctive smell of NaOCl/HOCl solution. Postoperatively, an outcome assessor of the local study group, who is unaware of the patient’s intraoperative intervention, will clinically assess the primary endpoint (SSI) on 3 postoperative study visits.

### Procedure for unblinding if needed {17b}

Unblinding of outcome assessors is permissible if significant hazards for patients’ safety or welfare occur. In such an unlikely case, the member of the study team responsible for the randomization procedure can unblind the outcome assessor for the randomization result of the concerned patient, only.

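### The emergency unblinding rule names the outcome assessor, who rates the primary endpoint, as the only recipient of the allocation

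*Protocol article*

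**What the plan says.** All references are to the protocol article.

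- **Procedure for unblinding if needed {17b}.** The section states: "Unblinding of outcome assessors is permissible if significant hazards for" the safety or welfare of patients arise. It calls this case unlikely. The person responsible for randomization "can unblind the outcome assessor for the randomization result of the concerned patient", and of no other patient. No treating physician or other recipient is named.
- **Who will be blinded {17a}.** "The blinding procedure is restricted to participating patients, the statistician who performs the final analysis and the outcome assessors". The assessor "will clinically assess the primary endpoint (SSI) on 3 postoperative study visits". For the operating team: "Blinding of the surgical team that performs the intervention is impossible because of the distinctive smell of NaOCl/HOCl solution".
- **Concealment mechanism {16b}.** Those with access to the randomization tool do no postoperative study visits. "After informing the surgical team of the randomization result", the printed sheets "must be stored away from the patient records, study documents and ISF to ensure blinding of the rest of the local study team".
- **Visit 3 to 5.** The assessor is described as independent, blinded and trained in CDC classification of SSI. No treatment role is given.
- **Strategies to improve adherence to interventions {11c}.** The irrigation is a single intraoperative act.

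**The concern.** Unblinding in an emergency normally serves whoever must act on the emergency. Here the rule sends the information to the person who rates the endpoint. The protocol cannot blind the surgeons, so the credibility of the SSI comparison depends heavily on the assessor not knowing the arm. The concealment section protects exactly this by keeping the randomization sheets out of the records.

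Some of the SSI criteria in Table 1 call for judgement, for example whether there is other evidence of infection in the deep incision or the organ/space. A rater who knows the arm can lean either way on such a criterion. At stake is detection bias in the primary endpoint for the patients concerned, and in SSI class, which is a secondary endpoint.

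**Working it through.** **1. Who needs the allocation, and who already has it**

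| Party | Knows the arm? | Stated role after surgery |
|---|---|---|
| Operating team | Yes ({16b}, {17a}) | Routine care; the attending surgeon's diagnosis also counts as SSI (Table 1, last line) |
| Randomizing team member | Yes ({16b}) | No postoperative study visits |
| Outcome assessor | No ({17a}) | Blinded SSI rating on days 5, 10 and 30 |
| Patient | No ({17a}) | May report the endpoint by telephone at visit 5 ({18b}) |
| Physician treating a later hazard, if not from the operating team | Not stated; the sheets are kept out of the patient records ({16b}) | Treats the hazard; an outside physician may complete the visit 4 or 5 form ({18b}) |

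The assessor is the only party in {17b} who may be told, and has no stated task for which the arm is needed. No study treatment remains to be stopped after surgery. The only party who might need the arm and lack it is a treating physician from outside the operating team, and {17b} does not mention that person.

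**2. What is exposed**

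The primary endpoint is any SSI within 30 days. If an SSI was recorded before disclosure, the binary endpoint is already fixed for that patient. Death before day 30 counts as SSI by rule ({20a}). What remains is a patient who is unblinded alive, with no SSI yet recorded and at least one visit to come.

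**3. The design figures**

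Inputs from Sample size {14}: SSI rates 16% and 4%, one-sided 2.5%, 80% power, two looks, efficacy bounds 2.963 and 1.969, interim futility bound 0.555, continuity correction, 20% drop-out.

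- Fixed design, unpooled variance: n = (0.16 × 0.84 + 0.04 × 0.96) × (1.960 + 0.842)² / 0.12² = 94.2 per group.
- Times the group-sequential inflation factor 1.056: 99.4.
- Continuity corrected: (99.4 / 4) × [1 + √(1 + 4 / (99.4 × 0.12))]² = 115.5, so 116 per group and 232 in all, as stated.
- Drop-out: 232 / 0.80 = 290, as stated.

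Expected events at these rates: 116 × 0.16 = 18.6 and 116 × 0.04 = 4.6, in total about 23.

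**4. Can one rating matter?**

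This is an illustration with the uncorrected pooled z, 116 per group and final bound 1.969: z = [(y − x) / 116] / √[2p(1 − p) / 116], where p = (x + y) / 232, x = experimental events and y = control events.

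| Experimental | Control | z | Passes 1.969? |
|---|---|---|---|
| 7 | 16 | 1.977 | Yes |
| 8 | 16 | 1.72 | No |
| 8 | 17 | 1.91 | No |
| 8 | 18 | 2.081 | Yes |

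Starting from 7 versus 16, one additional SSI rated in the experimental arm reverses the conclusion. At the planned rates the result is not borderline: 5 versus 19 gives z = 3.02. The illustration shows sensitivity near the boundary. It does not estimate bias.

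**The case against.** The case against is substantial, and most of it limits the point without removing it.

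- **The assessor is not the only person who must stay blinded.** A reader might infer this, but {17a} also blinds patients and the final statistician. The assessor is the key blinded person for ascertaining the endpoint.
- **The rule does not order or routinely cause disclosure.** It permits it, for one patient at a time, in a case called unlikely.
- **Unblinding need not cluster in the sickest patients or in those with SSI.** The background section does describe organ/space SSI as potentially life-threatening, so the inference is tempting. The protocol does not equate its trigger with SSI. Under Explanation for the choice of comparators {6b} it expects harm only from accidental contamination of a solution. Severe infections will also often meet criteria based on culture, reoperation or imaging, which leave less room for judgement.
- **A complete absence of safety benefit is not shown.** A later treating physician may not know the arm. That is a reason to tell that physician and gives none for telling the rater.
- **Dividing one event by the expected events does not measure this problem.** The same fraction applies to any single misclassification, whatever its cause.
- **The article's silence on later handling is not a defect.** A reader might infer that the unblinded assessor carries on and that the ratings are analysed as blinded. Reassignment or flagging may be set out in the full protocol.
- **Other routes for unblinded judgement exist.** Examples are the attending surgeon's diagnosis in Table 1 and the outside physician's form in {18b}. They do not justify adding another route, but they do constrain the remedy: moving the arm to the patient, or to a physician who then completes the SSI form, would only shift the leak.

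What stands is the rule as written: it names a recipient, and that recipient is the endpoint rater.

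**Conclusion.** The point holds in a limited form. {17b} permits one patient's allocation to go to the outcome assessor and names nobody else. On the stated roles this has no evident safety purpose, and it removes blinding for any SSI rating still to be made in that patient.

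The effect is probably small. It cannot be quantified, because the documents give no expected number of unblindings and no basis for how often knowledge of the arm would change a rating. It could matter only if an unblinded rating is changed and the result is close to the boundary, which with about 23 expected events can turn on a single patient. Sample size, boundaries and analysis are unaffected.

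The conclusion assumes that the assessor has no clinical task beyond what the article describes, and that the full protocol does not name a different recipient.

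**What to change.** Reword {17b} along these lines:

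1. In a safety hazard the randomizing team member releases the allocation to the physician treating the hazard. It is not released to the outcome assessor, nor by default to the patient.
2. An outside physician who has been told the arm does not complete the visit 4 or 5 SSI form where this can be avoided.
3. If an assessor is to be told the arm, SSI status is recorded first. If the assessor learns it some other way, status is recorded as soon as possible. The event is logged in the eCRF.
4. Another already trained, blinded assessor does that patient's remaining visits where one is available; {17a} and {17b} both speak of assessors in the plural. Otherwise the ratings are flagged for a sensitivity analysis.

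Reporting the number of unblindings by arm would let readers judge the size of the problem. If the full protocol already contains items 2 to 4, only the recipient needs changing. The cost is a few sentences and one eCRF field, with no added staff and no change in sample size.
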